#### Postoperative stroke

This complication is defined as any focal or global neurological syndrome occurring during the in-hospital stay caused by ischemia and/or hemorrhage not resolving within 24 h. The diagnosis and nature of stroke is made on the basis of findings at computed tomography and/or magnetic resonance imaging of the brain and confirmed by a neurologist. When neurological signs and symptoms disappear before discharge, stroke is defined temporary, otherwise it is defined as permanent.

#### Type 5 myocardial infarction

This adverse event is defined according to the recent definition criteria by Moussa et al. [15] as summarized in Table 8.

**Table 8 Tab8:** Definition criteria of type V myocardial infarction

*Baseline condition*	*Definition*
1. In patients with normal baseline CK-MB or cTn (I or T)	The peak CK-MB measured within 48 h of the procedure rises to ≥10 × the local laboratory upper limit of normal (ULN), or to ≥5 × ULN with new pathologic Q-waves in ≥2 contiguous leads or new persistent LBBB, *OR* in the absence of CK-MB measurements and a normal baseline cTn, a cTn (I or T) level measured within 48 h of the procedure rises to ≥70 × the local laboratory ULN, or ≥35 × ULN with new pathologic Q-waves in ≥2 contiguous leads or new persistent LBBB.
2. In patients with elevated baseline CK-MB (or cTn) in whom the biomarker levels are stable or falling	The CK-MB (or cTn) rises by an absolute increment equal to those levels recommended above from the most recent pre-procedure level.
3. In patients with elevated CK-MB (or cTn) in whom the biomarker levels have not been shown to be stable or falling	The CK-MB (or cTn) rises by an absolute increment equal to those levels recommended above plus new ST-segment elevation or depression plus signs consistent with a clinically relevant MI, such as new onset or worsening heart failure or sustained hypotension.

#### Delirium requiring drug treatment

Any postoperative neuropsychological syndrome requiring oral or intravenous drug treatment.

#### Blood loss 12 h after surgery

It refers to the amount of postoperative blood losses from mediastinal drainages within 12 h of surgery. Intraoperative blood losses are not taken in to account.

#### Hemoglobin nadir during the operation day

It refers to the lowest level of hemoglobin detected on the day of operation.

#### Hematocrit nadir during the operation day

It refers to the lowest level of hematocrit detected on the day of operation.

#### Highest postoperative creatinine level

It refers to the highest level of serum creatinine detected after surgery during the in-hospital stay.

#### Acute kidney injury

This end-point is defined as an increase in serum creatinine 1.5 -1.9 times the baseline level or serum creatinine increase≥26.5 μmol/l within seven days after surgery. This definition is according to the KIDGO criteria [16], but it considers only the change of postoperative serum levels of creatinine as outcome end-point. Therefore, acute kidney injury will be classified as listed in Table 9.

**Table 9 Tab9:** Grading of the severity of postoperative acute kidney injury

*Stages*	*Definition*
1	1.5–1.9 times baseline
	OR
	Serum creatinine increase ≥26.5 μmol/l
2	Serum creatinine 2.0–2.9 times baseline
3	Serum creatinine ≥3.0 times baseline
	OR
	Serum creatinine increase ≥353.6 μmol/l
	OR
	Initiation of renal replacement therapy

The need of renal replacement therapy is defined as temporary or permanent (in case the patient dies or is discharged on renal replacement therapy).

#### Red blood cell (RBC) units transfused intraoperatively

It refers to the amount of RBC units transfused intraoperatively (before the time “*at chest closure*”, see below). This does not refer to RBC units transfused before surgery or after the end of surgery.

#### RBC units transfused perioperatively

It refers to the overall amount of RBC units intra- and/or postoperatively transfused since the operation has started and till the day the patient is discharged home or to any other institution, i.e. intraoperative and postoperative. This does not refer to red blood cell transfused before surgery.

#### Use of fresh frozen plasma, solvent/detergent treated, pooled human plasma (Octaplas), platelets, rFVIIa, cryo-precipitate, fibrinogen and prothrombin complex concentrate

This refers to the use of these blood products used at the time of chest closure as well as after the operation until the day of discharge from the hospital. The amount of blood products are reported in homogenous units.

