#### Preoperative use of IABP

Preoperative insertion of IABP before the start of CABG. This refers to any IABP insertion during coronary angiography, percutaneous coronary artery intervention or in the operating room, but before skin incision.

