#### IABP

This refers to postoperative insertion of an intra-aortic balloon pump device.

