#### ECMO

This refers to intra- or postoperative insertion of an extracorporeal mechanical oxygenation device.

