#### Severity of postoperative bleeding

This will be graded according to the Universal Definition of Perioperative Bleeding (UDPB) in adult cardiac surgery [17]. Severe bleeding is defined as UDPB classes 3–4. Because of the complexity of this grading system, the E-CABG study group has developed its own grading system for a simple definition of severity of perioperative bleeding. The E-CABG investigators recognized that the amount of postoperative blood losses 12 h after surgery as defined by the UDPB criteria may not take into account the amount of intraoperative and postoperative bleeding occurring later on after surgery. Therefore the E-CABG investigators proposed a simple classification of perioperative bleeding based on the amount of RBC, platelets, fresh frozen/Octaplas units transfused during the intraoperative and postoperative period until the discharge. The methods adopted to stratify this outcome end-point are described in details in the paragraph “*Classification of the severity of postoperative complications occurring immediately after surgery*”.

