	Pericardial effusion requiring pericardial fenestration	4
	Acute kidney injury not requiring renal replacement therapy	4
	Transfusion of 5–10 units of RBC	5
	Reoperation for bleeding	5
	Deep sternal wound infection	5
	Postoperative IABP	5
Grade 3		
	Transfusion of > 10 units of RBC	7
	Renal failure requiring renal replacement therapy	7
	Mediastinitis	7
	Stroke	7
	Surgical or percutaneous procedure for technical failure	7
	Reoperation for hemodynamic instability	8
	Ventricular fibrillation/asystole	8
	Surgery for gastrointestinal complications	9
	Postoperative ECMO	9
Grade 4		
	In-hospital death	10

The E-CABG registry has been tailored to collect all the variables for stratification of perioperative bleeding according to the UDPB classification [17]. However, the latter classification is rather complicated and includes a rather large number of differed blood products for treatment and prevention of excessive bleeding. Its use can be limited by the inclusion in this stratification method of the amount of blood losses. In fact, time interval (12 h after surgery) is supposed to not capture the real amount of bleeding occurring after cardiac surgery. Therefore, extrapolating the medians of Table 10, the E-CABG investigators propose a grading of the severity of intra- and postoperative bleeding based on the type and amount of blood products transfused during surgery and the in-hospital stay as well as on the need of reoperation for bleeding (Table 12). The authors propose also an additive score to better grade the need to treat severe intra- and postoperative bleeding.

**Table 12 Tab12:** Grading and additive score for severity of intra- and postoperative bleeding as measured by the amount of blood products transfused and the need of reoperation for excessive bleeding

*Grades*	*Intervention for treatment of bleeding*	*Additive score*
Grade 0		
	No transfusion of blood products with the exception of 1 unit of RBCs	0
Grade 1		
	Transfusion of platelets	2
	Transfusion of fresh frozen plasma or Octaplas	3
	Transfusion of 2–4 units of RBC	3
Grade 2		
	Transfusion of 5–10 units of RBC	5
	Reoperation for bleeding	5
Grade 3		
	Transfusion of > 10 units of RBC	7

This classification included any transfusion of RBC, platelets, fresh frozen plasma and Octaplas occurred during surgery and after that, during the same in-hospital stay. Preoperative transfusions are not included in this classification

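### Plasma and platelets are defined from chest closure onward, but the E-CABG bleeding grade counts them throughout surgery; an intraoperative IABP is also not clearly assigned

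*Protocol article*

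**What the plan says.** **Blood products.** The protocol article defines the use of plasma, Octaplas, platelets, clotting-factor products and the like as follows: "This refers to the use of these blood products used at the time of chest closure as well as after the operation", continuing to the day of discharge. Two definitions earlier, intraoperative red cells are those given before a time point called chest closure. Perioperative red cells are counted from the start of the operation to discharge.

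The E-CABG bleeding grade uses a different window. *Severity of postoperative bleeding* bases it on the amount of RBC, "platelets, fresh frozen/Octaplas units transfused during the intraoperative and postoperative period until the discharge". The note under Table 12 agrees: "This classification included any transfusion of RBC, platelets, fresh frozen plasma and Octaplas occurred during surgery and after that, during the same in-hospital stay". Table 12 gives platelets 2 points and plasma or Octaplas 3 points, both Grade 1. The same items and weights appear in Table 11.

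**IABP.** The preoperative variable covers insertion at angiography, at PCI "or in the operating room, but before skin incision". The outcome variable reads: "This refers to postoperative insertion of an intra-aortic balloon pump device". The next definition, for ECMO, reads: "This refers to intra- or postoperative insertion of an extracorporeal mechanical oxygenation device". Table 11 gives postoperative IABP 5 points and Grade 2.

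**The concern.** A score can only use what its input variables hold. Here the score needs plasma and platelets from the whole operation, while the variable that feeds it starts at chest closure. A unit left out for that reason would look like a true zero and not like a missing value, so no later check for missing data would show it.

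The mismatch also touches the reason for having the grade. The article justifies its own classification partly on the ground that a 12-hour postoperative blood-loss measure may overlook intraoperative bleeding. Two of the three product types in the new grade would then be blind to that same period.

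Use of blood products, and postoperative need of IABP or ECMO, are also listed as main immediate end-points. The ambiguity therefore reaches beyond the two scores.

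**Working it through.** No sample size, power or alpha figure is involved. The check sets the windows side by side and then adds the published weights.

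**Step 1: windows as printed**

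| Item | Recording definition | Window needed by Tables 11 and 12 | Match |
|---|---|---|---|
| RBC | start of operation to discharge | surgery and after | yes |
| Platelets, plasma, Octaplas | chest closure to discharge | surgery and after | no |
| ECMO | intra- or postoperative insertion | labelled postoperative | covered by the definition |
| IABP | before skin incision (preoperative); postoperative insertion (outcome) | labelled postoperative | incision to end of surgery not assigned |

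**Step 2: can chest closure mean the whole operation?** No. The intraoperative red-cell definition uses it as the cut-off before which units count as intraoperative, and refers the reader forward for the term. The next use of the term is in the plasma and platelet definition. Read together, that definition leaves out the period that the red-cell definition calls intraoperative.

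**Step 3: points at stake for blood products.** Weights are from Table 12. The platelet and plasma items are scored as given or not given, whatever the amount, so a product loses its points only if all of it was given before chest closure.

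- Platelets only: 2 - 0 = 2 points lost.
- Plasma only: 3 - 0 = 3 points lost.
- Both: 2 + 3 = 5 points lost.
- Table 12 maximum: 2 + 3 + 7 (more than 10 RBC units) + 5 (reoperation for bleeding) = 17, so the loss is at most 5 of 17.

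**Step 4: when the bleeding grade changes.** Platelets and plasma are Grade 1 items. A patient with 2-4 RBC units is Grade 1 anyway. With 5-10 units or reoperation for bleeding the patient is Grade 2, and with more than 10 units Grade 3. So the grade falls, from 1 to 0, only if all plasma and platelets were given before closure, the patient had 0-1 RBC unit and there was no reoperation for bleeding. In all other affected patients only the additive score changes.

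**Step 5: frequency.** The document gives none. Let *p* be the share of patients whose plasma and platelets were all given before closure, and *q* the share of those with 0-1 RBC unit and no reoperation. The share regraded is *p* × *q*. With an assumed *p* of 3%:

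- *q* = 0: 0%
- *q* = 0.5: 0.03 × 0.5 = 1.5%
- *q* = 1: 3%

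The value of *p* is therefore an upper bound on grade changes, and the 3% is purely illustrative.

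**Step 6: IABP.** If an intraoperative insertion is the only event, Table 11 gives 5 points and Grade 2 when it is counted, and 0 points and Grade 0 when it is not. Combined with the largest loss in Step 3, the Table 11 sum can differ by 5 + 5 = 10 points, the weight given to in-hospital death.

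**The case against.** **Loss of data is not shown.** A reader might infer that plasma and platelets given earlier in the operation are in fact unrecorded. The document does not establish this. The score states its own window correctly in two places, and the Access datasheet, which decides what is entered, is not shown. This objection stands: the finding is a conflict between two definitions, and loss follows only where data are entered by the narrower one.

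**Intraoperative events in general are not lost.** A reader might also infer that the scores miss the intraoperative period as a whole. They do not, since intraoperative red cells and ECMO are covered by their definitions.

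**The IABP wording can be read generously.** The end-point list speaks of postoperative need of IABP or ECMO, which a device placed in theatre and still in use afterwards may meet. The article also labels ECMO postoperative in Table 11 while defining it as intra- or postoperative, so the label alone does not exclude intraoperative insertion. A centre could reasonably code any insertion after skin incision as postoperative. This weakens the claim that such a device belongs to no category. What remains is that adjacent definitions differ in wording and that centres may code differently.

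**Bias is not demonstrated.** It is tempting to say that the error varies with centre habits or operative technique and so distorts comparisons. Nothing in the document reports when these products or devices are used at each centre. Differential error is possible but not shown.

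**Consequences are limited.** Bleeding is also graded by UDPB, and primary end-points are set study by study. For blood products, the grade change is confined to the step between Grades 0 and 1. This is fair and bears on weight, but it does not remove the contradiction.

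**Conclusion.** The main point holds as a contradiction. The plasma and platelet variable begins at chest closure, whereas the bleeding grade built on it needs the whole operation. Where the variable definition is followed, a patient given these products only before closure loses 2 to 5 additive points. Such a patient moves from bleeding Grade 1 to Grade 0 if there was 0-1 RBC unit, no reoperation for bleeding and no plasma or platelets later. The result rests on the printed weights and on reading chest closure as the red-cell definition uses it. The frequency is unknown, and no percentage of misgraded patients can be derived from the document.

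The IABP point is secondary. Insertion between skin incision and the end of surgery is not clearly assigned, and up to 5 points and Grade 2 of Table 11 depend on how a centre reads the definition.

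**What to change.** 1. Give the plasma, Octaplas and platelet definition the window used for perioperative red cells: from the start of the operation until discharge. If use at chest closure is needed for another purpose, keep it as a separate field.
2. In the IABP outcome definition, state that insertion after skin incision is counted, in parallel with ECMO, and apply this to the Table 11 item. Leave Table 10 as reported, because it records a completed scoring exercise by 24 surgeons that cannot be redefined afterwards.
3. Have each centre check the patients already entered against local transfusion and operative records. This must be done at the centres, since the data sent for merging carry no patient identification code. It should be finished before the first analyses, which the article expects in July 2015.

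The cost is two reworded definitions, one or two datasheet fields and a look-back over patients recruited since January 2015.

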#### Severity of postoperative bleeding

This will be graded according to the Universal Definition of Perioperative Bleeding (UDPB) in adult cardiac surgery [17]. Severe bleeding is defined as UDPB classes 3–4. Because of the complexity of this grading system, the E-CABG study group has developed its own grading system for a simple definition of severity of perioperative bleeding. The E-CABG investigators recognized that the amount of postoperative blood losses 12 h after surgery as defined by the UDPB criteria may not take into account the amount of intraoperative and postoperative bleeding occurring later on after surgery. Therefore the E-CABG investigators proposed a simple classification of perioperative bleeding based on the amount of RBC, platelets, fresh frozen/Octaplas units transfused during the intraoperative and postoperative period until the discharge. The methods adopted to stratify this outcome end-point are described in details in the paragraph “*Classification of the severity of postoperative complications occurring immediately after surgery*”.

#### Early repeated revascularization

This refers to any CABG and/or PCI performed during the same hospital stay for any graft and/or stent-related complication as well as for progression of coronary artery disease.

#### Gastrointestinal complications

This refers to any gastrointestinal complication requiring endoscopy and/or surgical treatment.

#### Length of stay in the intensive care unit

This refers to the number of days the patient was treated in the intensive care unit (ICU) after surgery. Readmission to ICU is also taken in to account in the estimation of ICU stay.

#### Length of in-hospital stay

This refers to the number of days the patient was treated from the day of operation till the day of discharge from the hospital to any rehabilitation unit or home.

#### In-hospital death

It refers to any death occurred in during the same hospital stay in the Institution where CABG was performed.

#### Late death

This refers to death occurring after discharge due to any cause. Specific causes of death are collected to better define whether death is related to any cardiovascular cause.

#### Late stroke

This refers to any focal or global neurological syndrome occurring after discharge and caused by ischemia and/or hemorrhage not resolving within 24 h. The diagnosis and nature of stroke is made on the basis of findings at computed tomography and/or magnetic resonance imaging of the brain and confirmed by a neurologist.

#### Late myocardial infarction

This refers to any myocardial infarction occurring after discharge and requiring medical or revascularization treatment. Since the current definition of type V myocardial infarction requires adequate validation, only myocardial infarction occurring after discharge will be considered as late myocardial infarction.

#### Late repeated revascularization

This refers to any CABG and/or PCI performed after discharge for graft and/or stent-related complication as well as for progression of coronary artery disease.

#### Combined outcome end-point

This refers to any of the main outcome end-point (all-cause mortality, stroke, myocardial infarction and/or repeat revascularization) occurring any time after CABG. Since the current definition of type V myocardial infarction requires adequate validation, only myocardial infarction occurring after discharge will be considered in this end-point.

### Classification of the severity of postoperative complications occurring immediately after surgery

Adult cardiac surgery is associated with significant immediate postoperative mortality. Indeed, early mortality is generally considered a hard outcome end-point, and often the only one, of any analysis evaluating the outcome of cardiac surgery. However, the incidence of non-fatal complications after major surgery is rather high and may have a negative impact on patient’s recovery and the burden of resources necessary to treat such complications. Furthermore, postoperative complications may have a significant impact also on late survival [18–20].

The need of a grading system of postoperative complications has been recognized in surgery as a measure and a means to improve the quality of health care delivery [21]. Therefore valuable ranking systems have been developed for the assessment of quality of surgical treatment as well as a reproducible tool in clinical research [21, 22]. However, the existing ranking systems are more suitable for patients undergoing non-cardiac surgery as they take into account minor complications which are very frequent in patients undergoing adult cardiac experience and which can be considered of minor prognostic importance in this subset of patients. Therefore, any method for grading the severity and prognostic implications of postoperative complications should be specifically tailored for adult cardiac surgery.

There are objective difficulties in ranking the postoperative complications after cardiac surgery as they may be related to a number of preoperative risk factors and perioperative treatment methods and importantly, relevant complications have not been thoroughly investigated in large clinical series. Therefore, there is a lack of data for a proper weighting of the prognostic impact of postoperative complications. Indeed, previous ranking methods used in non-cardiac surgery were not derived from statistical analyses of clinical datasets, but rather were proposed by a few experienced clinicians based on the current knowledge of the clinical impact of any minor and major postoperative complication. A more reliable method to stratify the clinical impact of any complications would be to retrieve the evidence of the negative impact of postoperative complication through meta-analytical methods. However, data for meta-analysis could be limited to a few major complications and may be lacking for many others.

The E-CABG investigators have selected 25 complications or interventions for their treatment (Table 10), which are believed to have a prognostic impact and possibly associated with increased resources for their treatment. These investigators recognized that in many cases, an intervention performed for any complication would provide a better stratification measure than considering the complication itself. Because of this, a number of complications are herein defined as any intervention performed for their specific treatment. These investigators decided to not enlist here some postoperative adverse events because of intrinsic difficulties in defining their true nature (for example: pneumonia, type V myocardial infarction, sepsis), because they are secondary to other more significant adverse events (for example: prolonged tracheal intubation) or any time interval may not capture the real extent of the event (for example: postoperative blood losses). These investigators recognized also the difficulty in identifying a valid definition of postoperative low-cardiac output syndrome. In fact, thermodilution catheter is not routinely used in many centers and the use of a cutoff of postoperative cardiac index to define this event is thus not feasible. Furthermore, postoperative use of inotropes varies significantly between institutions as their use after cardiac surgery is not limited to the treatment of markedly decreased cardiac index. Therefore, in this registry the definition of postoperative severely depressed cardiac function is reserved only to those conditions requiring postoperative insertion of IABP or ECMO.

**Table 10 Tab10:** Mean, median and interquartile range of score assigned by 24 cardiac surgeons to 25 significant postoperative complications or interventions for their treatment

*Postoperative complication or intervention*	*Mean score*	*Median score*	*Interquartile range*
Transfusion of 1 unit of RBC	0.5	0.5	1.0
Transfusion of 2–4 units of RBC	2.7	2.5	1.0
Transfusion of 5–10 units of RBC	5.2	5.0	2.0
Transfusion of > 10 units of RBC	7.2	7.0	1.0
Reoperation for bleeding	4.6	5.0	1.75
Transfusion of platelets	2.7	2.0	1.75
Transfusion of fresh frozen plasma or Octaplas	2.7	3.0	1.75
Pericardial effusion requiring pericardial fenestration	3.9	4.0	1.0
Postoperative use of antibiotics	1.9	2.0	1.0
Atrial fibrillation	2.3	2.0	2.0
Ventricular fibrillation/asystole	6.8	8.0	3.0
Administration of inotropics > 12 h	3.9	4.0	2.0
Acute kidney injury not requiring renal replacement therapy	3.6	4.0	1.75
Renal failure requiring renal replacement therapy	6.7	7.0	1.75
Deep wound infection of the leg	2.9	3.0	2.0
Deep sternal wound infection	5.0	5.0	2.75
Mediastinitis	6.6	7.0	3.75
Permanent pace-maker implantation	3.3	3.0	2.0
Surgery for gastrointestinal complications	8.1	8.5	1.0
Stroke	7.4	7.0	1.0
Postoperative IABP	5.0	5.0	2.0
Postoperative ECMO	8.6	9.0	1.0
Surgical or percutaneous procedure for technical failure	7.1	7.0	2
Reoperation for hemodynamic instability	7.5	7.5	1
In-hospital death	10.0	10.0	0

Twenty-four E-CABG investigators have stratified the prognostic and severity burden of these 25 complications or interventions for their treatment giving a score from 0 to 10 to each of these adverse events/interventions. A score of 10 was supposed to measure the worst postoperative complication, i.e. patient’s death. Table 10 summarizes the mean, median and interquartile range of these scores.

The medians of these score were used to stratify the prognostic importance of each complication or intervention for its treatment (Table 11). Transfusion of one unit of RBC was considered not a significant event as both its mean and median scores were below 1. These investigators proposed a four grades classification method of postoperative complications in order to classify them according to their increasing severity. The fourth grade includes only the worst postoperative complication, i.e. patient’s death. Multiorgan failure was not herein considered a postoperative adverse events as this grading system includes most of the components of this syndrome. Table 11 summarizes also additive scores which are the rounded medians of Table 10. The sum of these scores for each complication/intervention occurring after CABG will be used as an additive score for further stratification of the prognostic importance of these events in each patient.

**Table 11 Tab11:** Grading and additive score for postoperative complications or interventions for their treatment

*Grades*	*Postoperative complications or interventions*	*Additive score*
Grade 0		
	None of the below mentioned complications/interventions	0
Grade 1		
	Postoperative use of antibiotics for proven or suspected infection	2
	Atrial fibrillation	2
	Transfusion of platelets	2
	Transfusion of fresh frozen plasma or Octaplas	3
	Transfusion of 2–4 units of RBC	3
	Deep wound infection of the leg	3
	Permanent pace-maker implantation	3
Grade 2		
	Pericardial effusion requiring pericardial fenestration	4
	Acute kidney injury not requiring renal replacement therapy	4
	Transfusion of 5–10 units of RBC	5
	Reoperation for bleeding	5
	Deep sternal wound infection	5
	Postoperative IABP	5
Grade 3		
	Transfusion of > 10 units of RBC	7
	Renal failure requiring renal replacement therapy	7
	Mediastinitis	7
	Stroke	7
	Surgical or percutaneous procedure for technical failure	7
	Reoperation for hemodynamic instability	8
	Ventricular fibrillation/asystole	8
	Surgery for gastrointestinal complications	9
	Postoperative ECMO	9
Grade 4		
	In-hospital death	10

The E-CABG registry has been tailored to collect all the variables for stratification of perioperative bleeding according to the UDPB classification [17]. However, the latter classification is rather complicated and includes a rather large number of differed blood products for treatment and prevention of excessive bleeding. Its use can be limited by the inclusion in this stratification method of the amount of blood losses. In fact, time interval (12 h after surgery) is supposed to not capture the real amount of bleeding occurring after cardiac surgery. Therefore, extrapolating the medians of Table 10, the E-CABG investigators propose a grading of the severity of intra- and postoperative bleeding based on the type and amount of blood products transfused during surgery and the in-hospital stay as well as on the need of reoperation for bleeding (Table 12). The authors propose also an additive score to better grade the need to treat severe intra- and postoperative bleeding.

**Table 12 Tab12:** Grading and additive score for severity of intra- and postoperative bleeding as measured by the amount of blood products transfused and the need of reoperation for excessive bleeding

*Grades*	*Intervention for treatment of bleeding*	*Additive score*
Grade 0		
	No transfusion of blood products with the exception of 1 unit of RBCs	0
Grade 1		
	Transfusion of platelets	2
	Transfusion of fresh frozen plasma or Octaplas	3
	Transfusion of 2–4 units of RBC	3
Grade 2		
	Transfusion of 5–10 units of RBC	5
	Reoperation for bleeding	5
Grade 3		
	Transfusion of > 10 units of RBC	7

This classification included any transfusion of RBC, platelets, fresh frozen plasma and Octaplas occurred during surgery and after that, during the same in-hospital stay. Preoperative transfusions are not included in this classification

